## Methods/design

### Study design

The Colorado LEAP project is a longitudinal cohort study utilizing a controlled quasi-experimental design in 5 rural Colorado communities. Two communities serve as intervention communities with the other 3 as matched controls. Intervention sites will receive *The Food Friends®* nutrition and physical activity programs in preschool and ‘booster’ programming in kindergarten and 1^st^ grade. Assessments will be administered 4 times - twice in preschool (Fall and Spring) and once in both kindergarten and 1^st^ grade (Spring) (Figure 1). Observational measures of children will be conducted at the school; parent/home measures will be sent home and returned to school via the child; and school personnel will complete school environment and policy assessments. This study was approved by the institutional review boards at Colorado State University and the University of Colorado Denver Anschutz Medical Campus.

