### Sample size estimation

This study is powered on mean change differences in gross motor skills between intervention and control children. The statistical evaluation associated with the research questions will employ either Multivariate Analysis of Variance (MANOVA) or Analysis of Variance (ANOVA) procedures followed by planned comparison t-tests. As such, a power analysis based on the formulas and tables proposed by Cohen [20] shows that to evaluate motor performance in children using the results of ANOVAs on gross motor measures reported by Bellows et al. [16], a sample size of 90 per group could detect significant differences in motor performance between the two groups with 90% power. A power analysis for changes in BMI with an improvement of .5 standard deviation by the intervention group over the control group (ES = .50) and a power level set at .80 would need a sample size of 64 per group to show statistical significance at α = .05. Further, because differences in assessing changes in food exposure have been detected in samples as low as n = 12, the power for this study was based upon motor skills. Thus, with 90 children per group the power is high enough to detect changes in motor performance while also having a sensitive environment to pick up effects on the nutrition measures. Finally, to account for potential 10% attrition rate, as seen in our previous studies, we are planning a potential study size of 200 children; that is, 100 children in each of the two convenience samples.

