### Physical activity

#### Physical activity levels and intensity

Pedometers and accelerometers will used to assess physical activity (PA). Two Walk-4-Life pedometer (Model W4L Classic; Plainfield, IL), with safety strap, will be sent home along with a log to record the number of daily steps. Parents will be asked to place the pedometer on the child and themselves when the child/parent gets out of bed and to take it off when the child/parent goes to bed. They will be asked to record the number of total steps taken each day for six days – four weekday and two weekend days. Parents will also be asked to record notes about if the child/parent did not wear the pedometer for a specific time during the day, what types of activities they participated in, etc. A subsample of participants will be asked to wear an Actical accelerometer (Phillips – Respironics, Oregon, USA) to measure time spent in various intensities of PA as well as time spent in activity at school versus home. The accelerometer will be attached on the non-dominant wrist of each student with semi-non-removable band to measure PA. The Actical is a small, lightweight, waterproof, omni-directional accelerometer. It will be placed on the child during the school day. Children will be asked to wear the accelerometer for a 6-day period and to maintain “typical” activity patterns. To encourage compliance in wearing the accelerometers, the children and parents will be given written and verbal instructions.

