### Data analysis

Data will be analyzed using SPSS 21.0 Windows (IBM SPSS Statistics, Inc., Chicago, IL) program. Descriptive statistics (e.g., percentage, mean, standard error, etc.) will be obtained for demographic, anthropometric, and weight status variables. Additionally, shape-based statistics will be calculated to test assumptions for parametric procedures; data not meeting assumptions will either be transformed or appropriate non-parametric procedures will be utilized. The statistical evaluation associated with the research questions will employ either MANOVA or ANOVA procedures followed by planned comparison t-tests. For example, to answer Question 1 that states *Food Friends®* and *Mighty Moves*™ increase willingness to try new foods and develop motor performance, and that these gains will persist throughout a three year period, a 2x2 MANOVA mixed model design will be used to assess the final outcome measures at the end of the last year. The two factors, are Treatment Intensity (2 levels; experimental and control groups), a between group factor, and Time (2 levels; pre and post treatment), a within group factor. The multiple dependent measures to be explored include the nutrition measures of food preferences, willingness to try, and dietary consumption along with physical activity measures including for example, gross motor skills, pedometer steps and accelerometer outputs. To test the specific hypotheses for Question 1, each dependent variable will be explored using 2x4 ANOVA design (the same factors as above but the within factor, Time, consisting of 4 time periods) followed by orthogonal *a priori* t-tests. Covariates will also be added to the basic ANOVA design to explore effects of age, sex, ethnicity, and location. The significance level will be set at α = 0.05 for all analyses.

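### The joint Question 1 MANOVA lists accelerometer outputs that only a subsample of unstated size will provide, so the planned 90 per group does not apply to that test

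*Protocol article*

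**What the plan says.** For Question 1 the Data analysis section of the protocol article states that "a 2x2 MANOVA mixed model design will be used to assess the final outcome measures at the end of the last year". It defines two factors: group (experimental or control) between children, and time (pre and post treatment) within children. The dependent measures named for this test are food preferences, willingness to try and dietary consumption, together with "physical activity measures including for example, gross motor skills, pedometer steps and accelerometer outputs".

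The section on physical activity levels and intensity says of the accelerometer: "A subsample of participants will be asked to wear an Actical accelerometer". It gives neither the size of the subsample nor how it is chosen. Pedometer steps come from a log that parents keep at home for six days.

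The Data analysis section then adds a second layer: "To test the specific hypotheses for Question 1, each dependent variable will be explored using 2x4 ANOVA design". The four times are those of the Study design section: "Assessments will be administered 4 times - twice in preschool (Fall and Spring) and once in both kindergarten and 1"st grade.

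The Sample size estimation section says "This study is powered on mean change differences in gross motor skills between intervention and control children" and that "a sample size of 90 per group could detect significant differences in motor performance between the two groups with 90% power". The step to 100 per group is explained by "Finally, to account for potential 10% attrition rate, as seen in our previous studies".

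**The concern.** The two statements about accelerometry do not fit together. If the outcome vector includes a variable that most or many children are never asked to provide, those children cannot enter a classical MANOVA, however complete their other data are. The first-named test for Question 1 would then run on the accelerometer subsample, reduced further to children whose pedometer log came back. A reader who sees 90 per group in the sample size section would assume that this number stands behind the joint test, and it does not.

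A second, weaker point concerns the 2x4 ANOVA. A classical repeated-measures ANOVA keeps only children seen at all four assessments, which run from preschool to the spring of 1st grade. The sample size provides for one overall loss of 10%, so it matters whether that allowance leaves any room.

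**Working it through.** **Inputs from the protocol article.** Sample size estimation: 90 per group at 90% power for motor performance; 10% attrition; 100 per group, 200 in total; for BMI, effect size 0.50, power 0.80 and 64 per group. Data analysis: alpha 0.05. Study design: four waves. Not given: the motor effect size and the accelerometer fraction.

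**The plan's own figures.** All checks use a two-sample t-test at two-sided alpha 0.05, with noncentrality d × √(n/2) and 2n − 2 degrees of freedom.
- BMI: d = 0.50 at 80% power gives 63.8, so 64 per group. This reproduces.
- Attrition: 90 / (1 − 0.10) = 100 per group, 200 in total. This reproduces.
- Motor: 90 per group at 90% power cannot be re-derived, because the article takes the effect from an earlier study without stating it. Solving backwards gives d = 0.486 (normal approximation: (1.960 + 1.282) × √(2/90) = 0.483). This value is implied by the plan, not stated in it.

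**Joint MANOVA.** The number of complete vectors per group is at most 90 × f, where f is the accelerometer fraction. The fractions are assumptions:
- f = 75%: 67.5
- f = 50%: 45
- f = 25%: 22.5
- f = 20%: 18

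These are ceilings, before any unreturned pedometer logs. No power is attached to them, because MANOVA power depends on the number of outcomes and their correlations, which the article does not give.

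**Gross-motor 2x4 ANOVA.** This needs gross motor scores only, so f plays no part. Starting from 100 per group, with power at the back-solved d = 0.486 and no allowance for clustering by community:
- 10% total loss, as planned: 100 × 0.9 = 90, power 90%.
- 10% per year over two years (assumed): 100 × 0.9² = 81, power 87%.
- 10% at each of three intervals (assumed): 100 × 0.9³ = 72.9, about 73, power 83%.
- 10% total loss plus 5% independent missed visits at each of four waves (assumed): 100 × 0.9 × 0.95⁴ = 73.3, power 83%.

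The t-test on one contrast serves here as a yardstick for the planned comparison; it is not the power of the full 2x4 interaction.

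**The case against.** The strongest reply is that the powered analysis is untouched. The study is powered on gross motor skills alone, and each variable has its own 2x4 ANOVA, so the accelerometer subsample removes no child from the motor analysis. That stands. A reader might infer that the subsample pulls the study's main comparison well below 90 per group; the documents do not support this. Nor would it be right to evaluate the motor effect at the subsample sizes and quote the result as the power of Question 1: no planned single-outcome motor test is confined to the subsample, and such figures are not MANOVA power.

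It is also fair that 90 per group is already net of attrition, and that the article bases the 10% on its own earlier studies. A fall to 73 per group rests on losses that the article nowhere states.

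Third, the article does not mention listwise deletion, and missing-data rules are commonly left to a full analysis plan. Their absence is not held against the plan. Dropping incomplete records is, however, how the named procedures work, and the term mixed model in the article is defined as one between-group and one within-group factor, which is the classical design and not a likelihood-based model. A reader might go further and infer biased results from families who move or fail to return packets; the article gives nothing to show this.

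Finally, the list of measures is partly illustrative, and the article allows either MANOVA or ANOVA. One joint vector is therefore the likely reading and not a certain one. Even so, accelerometer outputs are named in the list.

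**Conclusion.** The concern holds in a limited form. As written, the joint 2x2 MANOVA for Question 1 includes an outcome collected only in a subsample of unstated size, so it can use at most that subsample and the 90 per group does not describe it. This follows from the two sections and from how a classical MANOVA works; only the size of the shortfall (about 18 to 68 per group remaining at 20% to 75%) rests on assumption.

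The gross-motor 2x4 ANOVA is not affected by the subsample. Its weakness is that a child missing one of four waves is dropped, while 90 / 0.9 = 100 leaves no slack beyond 10% total loss. If total loss stays at 10%, the planned 90% power stands. Power of about 83% with 73 per group is an example under assumed further loss and a back-solved effect, not a prediction. The point calls for a change to the analysis wording and does not put the powered comparison in doubt.

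**What to change.** Take accelerometer outputs out of the joint MANOVA and analyse them separately, labelled as the subsample, with its size stated. If the joint test is to keep them, state the number of children on which it will run.

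Analyse each Question 1 outcome with a linear mixed model with group, time as a four-level factor and their interaction, using all available measurements. This keeps children who miss a wave and is valid if data are missing at random. The planned comparisons can be taken as contrasts from the same model. Report the analysed number per group at each wave.

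The cost is small. The omnibus test no longer covers accelerometry, or is dropped, and there is minor extra analysis work. No outcome is lost, because the plan already gives each dependent variable its own analysis, and no data collection changes.

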*The Food Friends* program is one such intervention that has addressed developmental behaviors in young children. Comprised of two components *– Fun with New Foods®* and *Get Movin’ with Mighty Moves®* - the program has successfully demonstrated increases in both children’s willingness to try new foods (food preference) and gross motor performance in preschool-aged children [15,16]. Further exploration is warranted to understand social and environmental influences on these behaviors.

Children’s eating and activity behaviors are influenced by factors that are individual to the child, but also by the environments, in which they live, learn and play. Ecological models provide a framework for addressing interactions across individual, social and environmental spheres of influence [17,18]. Predictive behaviors within these environments can influence child behaviors. While many predictive behaviors have been shown to influence dietary intake, physical activity, and weight status; food preference and motor performance merit further exploration. Understanding the context in which child behavioral patterns are developed is critical to developing a model to address childhood obesity. Skouteris [19] makes the argument that children’s development is a bidirectional transaction, with parents influencing children but also children impacting parents’ decisions and behaviors. Understanding environments, parent behaviors and children’s behaviors over time will provide an opportunity to begin to develop transactional models.

The Colorado Longitudinal Eating And Physical activity (LEAP) Study utilizes a social ecological approach to explore individual, family and environmental factors and their relationship to child weight status over a 3 year timeframe. Our primary research questions are as follows:

1. Are behavior changes (e.g. increased willingness to try new foods and improved gross motor skills) positively influenced by a preschool nutrition and activity program, *The Food Friends®*, sustained through early elementary school?

2. Do *The Food Friends®* programs have an impact on reducing the percentage of children considered overweight and/or obese over a 3 year timeframe?

3. Do food preference and gross motor performance directly affect child weight status or are they mediators to dietary intake and physical activity?

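### A flat 0.05 level over at least six Question 1 outcomes, with no testing order and no priority for the powered outcome, leaves a 16% to 26% chance of a false positive if nothing works

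*Protocol article*

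**What the plan says.** The Background section introduces three questions with "Our primary research questions are as follows" and does not rank them. Sample size estimation then singles out one outcome: "This study is powered on mean change differences in gross motor skills between intervention and control children". It adds a supplementary calculation for BMI.

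For Question 1, the Data analysis section starts with an omnibus test: "a 2x2 MANOVA mixed model design will be used to assess the final outcome measures at the end of the last year", with time at two levels. The dependent measures are the "nutrition measures of food preferences, willingness to try, and dietary consumption along with physical activity measures", and the activity measures are illustrated by "gross motor skills, pedometer steps and accelerometer outputs". That makes six named measures, and the activity list is left open. Next, "each dependent variable will be explored using 2x4 ANOVA design", now with four time points, followed by preplanned orthogonal t-tests. The paragraph closes with "The significance level will be set at α = 0.05 for all analyses".

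No sentence makes the ANOVAs depend on the MANOVA, sets an order of testing, or gives gross motor skill a special place in the analysis.

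**The concern.** The sample size treats gross motor skill as the outcome that matters most, but the analysis lists it as one example among several, all tested at the same level. With six or more tests at 0.05, an isolated significant result on, say, pedometer steps is weak evidence that the programme works, and the plan gives a reader no means of telling it from a chance finding.

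This goes beyond detail that an article may leave to a fuller plan. The flat level is a stated rule, and a later analysis plan that adjusted for multiplicity would contradict it.

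**Working it through.** **Inputs from the protocol article**
- Level: 0.05 for every analysis (Data analysis).
- Question 1 outcomes: 3 nutrition + 3 activity = at least 6 (Data analysis).
- Powered outcome: gross motor skill, 90 per group for 90% power, no effect size given (Sample size estimation).
- Omnibus: one 2x2 MANOVA, not stated as a gate (Data analysis).

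**The plan's own figures**
- The BMI comparison at an effect size of 0.50 and 80% power "would need a sample size of 64 per group to show statistical significance at" α = .05. A two-sided two-sample t-test gives 63.8, so 64, and the figure reproduces. A one-sided test (normal approximation) would need 50, so I take the tests as two-sided.
- Attrition: 90 / (1 − 0.10) = 100 per group, 200 in total, as stated.
- The motor figure cannot be checked without its effect size. Solving backwards, 90 per group at 90% power, two-sided, implies d = 0.486.

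**Chance of at least one false positive, all nulls true, one test per outcome**

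Independent tests: 1 − 0.95^k.
- k = 6: 1 − 0.735 = 26.5%

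The outcomes are unlikely to be independent: willingness and liking come from the same tasting, and both activity devices measure movement. I therefore simulated equicorrelated normal test statistics (200,000 runs) and counted runs with any |z| above 1.96.

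| Correlation | 6 outcomes |
|---|---|
| 0 | 26.5% |
| 0.3 | 24.1% |
| 0.5 | 20.7% |
| 0.7 | 16.5% |

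**Larger counts (assumed; the article gives no number)**
- Four BOT-2 subtests in place of one motor score: 6 − 1 + 4 = 9 tests, 1 − 0.95^9 = 37.0% if independent.
- Three orthogonal contrasts over four time points for each outcome: 6 × 3 = 18 tests, 1 − 0.95^18 = 60.3% if independent; 56.4%, 50.4% and 41.6% at between-outcome correlations of 0.3, 0.5 and 0.7.
- Independent tests needed to pass 50%: ln 0.5 / ln 0.95 = 13.5, so 14.

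**Does the MANOVA protect the univariate tests?** It compares two time points while the ANOVAs use four, so it is not the omnibus of those tests. It is not written as a condition for them. Even as a gate, it would hold the error near 5% only if every null were true: once one outcome truly responds, the gate tends to open and the others are tested unprotected at 0.05.

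**Price of the alternatives.** Bonferroni over six outcomes sets 0.05 / 6 = 0.00833 each. At d = 0.486 and 90 per group, motor power falls from 90% to 72%, and about 132 per group would restore 90%. One confirmatory motor test at 0.05 leaves the sample size as it is.

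**The case against.** The best defence is that Question 1 centres on two behaviours, willingness to try new foods and gross motor skill, each targeted by its own programme component. Two independent tests at 0.05 give 1 − 0.95² = 9.75%. The wider list is described partly in the language of exploration, and the Discussion presents much of the work that way. This has some force, but the Data analysis section says the univariate tests serve Question 1's specific hypotheses and does not rank the outcomes. Even the two-test reading nearly doubles the nominal level.

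A reader might infer more than the article supports:
- **That a false positive is likely.** For the six named outcomes it is not more likely than not. Only the assumed count of 18 tests reaches about half or more.
- **That any one significant test would make the trial positive.** The article contains no success rule.
- **That three primary questions make the family much larger.** Question 3 is judged by changes in beta weights across models, which adds no defined significance test.
- **That Question 2 is a BMIz test.** It is worded as the share of children who are overweight or obese; BMIz is only listed as a calculated score.

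It is also fair that the article defines no single summary of the four BOT-2 subtests, so it cannot be confirmed which motor score the sample size rests on. That limits what can be said about power; it does not supply error control.

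**Conclusion.** The point stands as a matter that should be changed. The stated rule leaves the error across the six Question 1 outcomes at about 16% to 26%, roughly three to five times the nominal 5%, and the powered outcome has no priority in the analysis.

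The range assumes that every null is true, that there is one two-sided test per outcome, that each test holds its own 5% level, and that correlations run from 0.7 down to 0. The 37% and the 42% to 60% depend in addition on test counts that the article does not give, and should be read as illustrations.

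**What to change.** Replace the sentence on the significance level with a short paragraph that does the following:
1. Names one confirmatory test at 0.05: treatment by time on a single prespecified BOT-2 gross motor summary, with the time comparison fixed in advance.
2. Applies Holm across the other Question 1 outcomes, including willingness to try, and the Question 2 outcome as worded (share overweight or obese). With five named outcomes plus one, the smallest p-value is compared with 0.05 / 6 = 0.0083.
3. Reports BOT-2 subtests, remaining time contrasts and Question 3 as exploratory, with estimates and confidence intervals.

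As two separate families, the confirmatory test and the Holm set are each held at 0.05, which bounds the total at 0.05 + 0.05 = 0.10. If 0.05 overall is wanted, the Holm set should be tested only after the confirmatory test succeeds.

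The cost is one paragraph and less favourable p-values for the non-primary outcomes; willingness to try, which Question 1 names alongside motor skill, moves to the adjusted set. No more children are needed, and the stated motor power is kept, provided the chosen summary is the measure that the power calculation used.

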**Methods:**

The study is located in 5 rural Colorado preschool centers and elementary schools (2 treatment and 3 control). Treatment sites receive *The Food Friends®* nutrition (12 weeks) and physical activity (18 weeks) interventions during preschool. Observational measures assess 3 layers of the social ecological model including individual, family and organizational inputs. Children’s food preferences, food intake, gross motor skills, physical activity (pedometers/accelerometers), cognitive, physical and social self-competence and height/weight are collected. Parents provide information on feeding and activity practices, child’s diet, oral sensory characteristics, food neophobia, home food and activity environment, height/weight and physical activity (pedometers). School personnel complete a school environment and policy assessment. Measurements are conducted with 3 cohorts at 4 time points – baseline, post-intervention, 1- and 2-year follow-up.

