### Healthy growth

#### Anthropometrics

Children’s weight and height will be measured according the method of Harrison and colleagues [43] on a digital scale (Lifesource ProFit UC321; Milpitas, CA) to the nearest 0.05 kg (.1 pounds) and by portable stadiometer to the nearest 0.1 cm (Seca Corp, Hamburg, Germany) by trained research staff. Body Mass Index (BMI) and sex- and age-adjusted BMIz scores will be calculated in the manner documented in the 2000 CDC Growth Charts for the United States [44]. Parental height and weight is collected by self-report, and BMI is calculated.

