To assess whether preference and motor performance directly affect child weight status or serve as mediators to dietary intake and physical activity as they affect child weight (Question 3), three prediction models will be tested beginning with the use of a hierarchical multiple regression analysis. In both prediction models, measures representing concepts of Davison and Birch’s ecological model of child weight status serve as predictors (i.e. independent variables) with measures of child characteristics and child risk factors entered first (step 1), and measures of parenting styles and family characteristics in the next step, (step 2). The prediction models will differ in their inclusion or exclusion in step 1of (a) dietary intake and physical activity measures or (b) taste preference and motor performance or (c) the combination of dietary intake, physical activity measures, taste preference and motor performance. Changes in the beta weights of these variables across the 3 predictor models will be examined to determine the relationships of taste preference to dietary intake and motor performance to physical activity measures.

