## Discussion

Currently, studies are beginning to examine behaviors and correlates related to children’s weight status across multiple levels of the social ecological model [58], however most have been cross-sectional in nature [7,59]. Longitudinal studies are needed to identify causal influences of children’s dietary and physical activity behaviors as well as on growth [19]. Examining eating and activity behaviors longitudinally, and in multiple environments, can provide insights into relationships between predictive behaviors and dietary, physical activity and weight outcomes.

The Colorado LEAP study utilized Davison and Birch’s ecological model of childhood obesity as a springboard for the design of the study, which allows for longitudinal exploration of relationships among eating habits, physical activity patterns, and weight status within and across spheres of the social ecological model. The methods represent an advance in study design as they will allow not only for interaction among spheres but will do so predictively across time. In addition to the primary study outcomes examining behavior changes in children, the design allows for exploration into what parents report at baseline and its impact on child behaviors over time, and conversely child behaviors at baseline and the impact on parent response at future time points. Examining the data in this way supports Skouteris et al.’s [19] viewpoint of children’s development being bidirectional.

Key strengths of this study include utilization of a multi-disciplinary approach and a longitudinal design embedded within a social ecological framework. A further strength is that the recruitment strategy includes both boys and girls from ethnic minority populations in rural areas and will provide insights into obesity prevention effects on these at risk populations. It should be noted that while schools based in rural communities were purposefully chosen as study sites, a limitation is that we do not include a measure assessing the obeseogenic environment at the community level. Ultimately, the design of the Colorado LEAP Study has the potential to inform strategies for childhood obesity interventions in early childhood.

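### The Question 3 regressions of child weight status name no earlier BMI z-score and set no time order, so their betas can mix effects on weight with effects of weight

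*Protocol article*

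**What the plan says.** The Background lists Question 3 among the primary research questions: "Do food preference and gross motor performance directly affect child weight status or are they mediators to dietary intake and physical activity". The Data analysis section says that "three prediction models will be tested beginning with the use of a hierarchical multiple regression analysis". Every model has "measures of child characteristics and child risk factors entered first (step 1), and measures of parenting styles and family characteristics in the next step, (step" …). The models differ in whether step 1 holds "a) dietary intake and physical activity measures or (b) taste preference and motor performance", or all of these together. The conclusion is to be drawn as follows: "Changes in the beta weights of these variables across the 3 predictor models will be examined".

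Diet, physical activity, taste preference and motor performance are the only specific step 1 measures named. No earlier BMI, BMIz or weight status appears, change in BMIz is not given as the outcome, and no wave is stated for outcome or predictors. The covariates listed just before (age, sex, ethnicity, location) belong to the Question 1 ANOVA and do not include baseline weight either.

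The data exist. Under Anthropometrics, "Body Mass Index (BMI) and sex- and age-adjusted BMIz scores will be calculated", and the abstract states that "Measurements are conducted with 3 cohorts at 4 time points", the first of them baseline.

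**The concern.** The question is causal in wording, and the Discussion presents the study as an advance on cross-sectional work, saying of its methods that "they will allow not only for interaction among spheres but will do so predictively across time". A regression of weight level on behaviours, with no earlier weight and no time order, does not use that advantage. If heavier children score worse on a motor test, and heavy children tend to stay heavy, motor score will predict weight even when it has no effect on it.

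The measures make this plausible. The motor battery tests balance, speed and strength, on which body weight could bear. One scale of the feeding questionnaire records parents' concern about the child's weight, which could respond to existing weight; parenting measures enter in step 2.

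At stake is the answer to a primary question. A motor, preference or feeding beta could be read as a direct effect when it reflects weight already present. Comparing betas across the three models does not remove this, because the same unadjusted weight can lie behind the betas in each of them.

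**Working it through.** The plan gives no figure to reproduce here. The check has two parts: what the text fixes, and how large the mixing could be.

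**What the text fixes.** It sets the method, the two steps, the three variants and the basis of inference. It does not name earlier weight or the waves. A level-on-level regression without baseline BMIz would therefore comply with it.

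**Inputs.**
- n = 180: the sample size section gives 90 per group, and 2 × 90 = 180; equally, 200 less 10% attrition is 180.
- α = 0.05 from Data analysis. Sidedness is not stated; two-sided is assumed.
- Correlation of motor score with baseline BMIz, r: assumed, -0.1 to -0.4.
- Correlation of baseline with later BMIz (tracking), ρ: assumed, 0.6 to 0.9.
- True effect of motor score on later BMIz: zero, by construction.
- Motor score is the only behavioural predictor. This simplifies the planned multi-predictor models.

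**Without baseline BMIz.** The expected standardised motor beta is r × ρ. At r = -0.2 and ρ = 0.7 it is -0.2 × 0.7 = -0.14. Its standard error is about √((1 - 0.14²)/178) = √(0.9804/178) = 0.074, so the test statistic averages about -0.14/0.074 = -1.9. The critical value is 1.973, so slightly under half of studies would be significant.

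**With baseline BMIz.** The partial beta is (r_MY - r × ρ)/(1 - r²), where r_MY is the correlation of motor score with later BMIz. This is (-0.14 - (-0.2 × 0.7))/(1 - 0.04) = 0/0.96 = 0.

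**Simulation** (2000 replicates per setting, ordinary least squares; 4 of the 16 settings shown):

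| r | ρ | r × ρ | Beta without BMIz | Significant | Beta with BMIz | Significant |
|---|---|---|---|---|---|---|
| -0.1 | 0.6 | -0.06 | -0.062 | 13.2% | -0.001 | 4.8% |
| -0.2 | 0.7 | -0.14 | -0.140 | 48.0% | -0.001 | 5.4% |
| -0.3 | 0.8 | -0.24 | -0.237 | 90.0% | 0.002 | 4.0% |
| -0.4 | 0.9 | -0.36 | -0.359 | 99.9% | 0.001 | 4.6% |

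Over all 16 settings, the adjusted model rejected in 4.0% to 6.2% of replicates, which is nominal within simulation error.

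**The case against.** Four arguments carry weight.

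- **Open category.** A reader might infer that the plan excludes baseline weight. The document does not say so. Child characteristics and risk factors are not itemised, age and sex are not named for Question 3 either, and a fuller plan may list them all. This limits the point to what the text permits. It does not remove it, because the article does fix the structure of the models, and the causal reading depends on this covariate and on the time order.
- **The error rate.** A reader might take 48%, or the wider range in the table, as the false-positive rate of the Question 3 analysis. It is not. The simulated model has one behavioural predictor, whereas the planned models have many and one of the three omits motor performance. The plan also judges by changes in betas, not by a test of one beta, and no error rate was computed for that comparison. A confounded beta would still enter it.
- **Causal direction.** The same correlations arise if earlier motor skill lowered baseline weight. Then -0.14 is a real total effect, and adjustment removes it. The Background itself says that food preferences form before birth and in early childhood. Adjustment is therefore a choice of estimand, and the unadjusted model is not simply wrong.
- **Thin textual support.** The two-way influence that the article describes is between parent and child, not between weight and motor score. Strong tracking and an effect of weight on motor tests are assumptions here, and the remark about prediction across time describes the methods as a whole, not these regressions.

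**Conclusion.** The point holds in a limited form. The Question 3 models, as written, can be fitted without earlier BMIz and without time order. Fitted that way, they cannot separate behaviour affecting weight from weight affecting behaviour. Under the central assumptions (r = -0.2, ρ = 0.7, n = 180, a single predictor, no true motor effect) the spurious beta is about -0.14 and is significant in about 48% of studies, against about 5% with baseline BMIz in the model. The size depends wholly on correlations and a causal direction that the document does not give. It shows that the mixing could matter, not how often the planned analysis would err. This is a cheap improvement to a stated method.

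**What to change.** In the Question 3 paragraph of Data analysis, state that:

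- the outcome is 1st-grade BMIz;
- behavioural and parenting predictors come from an earlier wave than the outcome;
- preschool-Fall BMIz enters step 1 of all three models;
- the same models without it are reported alongside;
- the adjusted betas describe later weight given starting weight and do not count effects that acted before age 4.

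The time order and the adjustment belong together: adjusting for baseline weight helps only if the outcome is later and the predictors precede it.

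The cost is a few sentences and no new data collection. The downsides are one degree of freedom, the loss of children without a baseline height and weight, and the narrower estimand, which is why the unadjusted models should be kept in view. Adjustment does not remove other confounding or measurement error.
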